### Baseline questionnaire

The baseline questionnaire will include a total of nine items. Items 1–3 will investigate (1) age (continuous); (2) sex (female/male) and (3) relationship status (single/in a relationship). Items 4 − 7 will investigate outcome measures for (4) total weekly alcohol consumption during a typical week; (5) HED during the last month; (6) eBAC during the last month and (7) number of negative consequences caused by drinking alcohol during the last month. In addition, students will be asked to (8) state their goal for reducing their weekly alcohol consumption and in combination with question 8, they will receive feedback on their weekly alcohol consumption, based on their earlier response. Finally, students are asked to (9) specify the mobile phone number to which they wish to receive the SMS support.

### Follow-up questionnaires

The follow-up questionnaire will include four questions investigating the primary and secondary outcomes: (1) total weekly alcohol consumption during a typical week; (2) HED during the last month; (3) eBAC during the last month and (4) number of negative consequences caused by drinking alcohol during the last month.

### Statistical analyses

The baseline characteristics of responders will be compared between randomized groups using the chi-squared test or Fisher’s exact test for comparison of proportions, and Student’s *t* test for comparison of means. All outcome analyses will be compared between the two randomized groups (both with the same follow-up time) under the intention-to-treat principle (that is, all randomized individuals will be included in their originally randomized groups).

Total weekly consumption, eBAC and the number of negative consequences will be assessed for skewness by visual inspection of histograms or Q-Q plots. If skewed, they will be either log-transformed and analysed with linear regression or analysed with negative binomial regression. Frequency of HED occasions will be analysed by ordered logistic regression. All regression analyses will first be performed unadjusted, and then will be adjusted for weekly alcohol consumption at baseline, age, university and gender. If any of the baseline characteristics are significantly different between the two groups, further adjustment will be made to these covariates as well. The adjusted analyses will be the primary analysis. The data will be examined graphically for outliers. A sensitivity analysis excluding outliers will be performed.

Missing outcome data will be initially handled by a complete-cases analysis, which assumes that the data are missing at random (MAR). If data are not MAR, then non-responders differ systematically from responders and early responders are likely to differ systematically from late responders, who are likely to be similar to non-responders. Therefore, we will explore the plausibility of the MAR assumption by first regression of the primary outcome (weekly alcohol consumption) on the number of follow-up attempts needed before an individual responded.

Second, attrition will be investigated for significant differences between the study groups in completion of the follow-up questionnaire, and baseline characteristics will be compared between participants who do and do not respond at follow up. Any significant associations found could provide possible evidence against the MAR assumption.

Effect modification tests for total weekly consumption according to baseline, age, university, and gender will be undertaken for the primary outcome only. All analyses will be performed with two-sided tests with a 5% level of significance.

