### Outcome measures

The primary outcome measure will be total weekly alcohol consumption. This is computed as the sum of alcohol consumption for each of the 7 days in a typical week. Secondary outcomes will be frequency of heavy episodic drinking (HED), highest estimated blood alcohol concentration (eBAC) on one drinking occasion and the number of negative consequences caused by excessive drinking. All measures are based on the past month.

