### Power calculation

To detect an effect size of 15% standard deviations between the two groups at the 3-month follow up with a 5% significance level and 80% power, we require 699 individuals analysed per group, i.e. a total of 1398 individuals. Assuming a 3-month follow-up rate of 80%, we need 874 per group, i.e. a total of 1748 individuals.

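### The adjusted models for the three secondary outcomes do not prespecify the outcome's own baseline value, although it is collected, so precision is given up for no saving

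*Protocol article*

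**What the plan says.** The Statistical analyses section of the protocol article sets a single covariate list for all outcomes: "All regression analyses will first be performed unadjusted, and then will be adjusted for weekly alcohol consumption at baseline, age, university and gender". It then states: "The adjusted analyses will be the primary analysis". A further rule lets in other variables according to the data: "If any of the baseline characteristics are significantly different between the two groups, further adjustment will be made to these covariates as well".

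The Outcome measures section names the first two secondary outcomes: "Secondary outcomes will be frequency of heavy episodic drinking (HED), highest estimated blood alcohol concentration (eBAC) on one drinking occasion". The third is a count of drinking's negative consequences. The Baseline questionnaire section shows that all three are measured before randomisation, as items "5) HED during the last month; (6) eBAC during the last month and (7) number of negative consequences caused by drinking alcohol". The Follow-up questionnaires section repeats the same measures after three months: "The follow-up questionnaire will include four questions investigating the primary and secondary outcomes".

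**The concern.** An outcome's own baseline is usually its strongest single predictor, and adjusting for it is usually the cheapest way to gain precision in a randomised comparison. The common covariate list does this for the primary outcome only. Each secondary outcome is adjusted for the baseline of a different variable, while its own baseline sits unused in the same database.

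The significance-triggered rule does not fill the gap. It selects a covariate because the arms differ on it, not because it predicts the outcome. It also leaves the final model unknown until the data are seen. That matters for HED, where the planned model is ordered logistic: adding a strong predictor there changes the conditional odds ratio being estimated.

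At stake is the power of the three secondary hypotheses. These comparisons will probably rest on fewer people than the primary one, because the SMS and telephone follow-up described under Participants and procedure asks only about weekly consumption.

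**Working it through.** **The plan's own figure.** The Power calculation section begins: "To detect an effect size of 15% standard deviations between the two groups at the 3-month follow up". With two-sided α = 0.05 and 80% power, the normal approximation is n = 2(1.96 + 0.84)²/0.15² ≈ 698 per arm. The t-test version gives 698.6, so 699 as stated. Then 699/0.80 = 873.75, so 874 per arm and 1748 in total. The figure reproduces. It assumes no covariate adjustment, so the present point does not alter it.

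**How often the conditional rule would act.** Under randomisation, a 5% test of one baseline variable is significant in about 5% of trials. A simulation of 4,000 trials with 699 per arm gave 4.6%.

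**Assumed inputs.** The document gives no correlations. Let
- w = correlation of the follow-up outcome with baseline weekly consumption, 0.3–0.4;
- r = its correlation with its own baseline, 0.5–0.6;
- c = correlation between the two baselines, 0.5.

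Age, university and gender are left out of the calculation.

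**Formulae for a linear model.**
- R² with weekly consumption only = w².
- R² with both baselines = (r² + w² − 2rwc)/(1 − c²).
- Variance ratio = (1 − R² with both)/(1 − w²).
- For a comparison that has 80% power under the stated adjustment, power after adding own baseline = Φ(2.80/√ratio − 1.96).

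**All four corners, c = 0.5.**

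| r | w | R² with both | Variance ratio | Variance cut | Power |
|---|---|---|---|---|---|
| 0.5 | 0.4 | 0.21/0.75 = 0.280 | 0.720/0.84 = 0.857 | 14% | 86% |
| 0.5 | 0.3 | 0.19/0.75 = 0.253 | 0.747/0.91 = 0.821 | 18% | 87% |
| 0.6 | 0.4 | 0.28/0.75 = 0.373 | 0.627/0.84 = 0.746 | 25% | 90% |
| 0.6 | 0.3 | 0.27/0.75 = 0.360 | 0.640/0.91 = 0.703 | 30% | 92% |

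**Wider assumptions.** Over r 0.4–0.7, w 0.2–0.4 and c 0.4–0.6, the standard error falls in every case. The fall runs from 2.4% (r = 0.4, w = 0.4, c = 0.6) to 32.7% (r = 0.7, w = 0.2, c = 0.6). In the middle case (r = 0.5, w = 0.3, c = 0.5) it is 9.4%. Power for 0.15 SD with 699 per arm then rises from 83.6% to 90.1%; simulation gave 82.8% and 89.1%. The starting value exceeds 80% because adjustment for weekly consumption already helps.

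**The case against.** The best defence is that nothing here is invalid. One covariate set for all outcomes is a defensible simplification, the document claims no power for the secondary outcomes, and an analysis plan not shown may refine the models. All of this is fair, and it limits the weight of the point. It does not remove it: the article does not leave the covariates open but lists them and applies the list to every regression.

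The size is also open to challenge, and much of that challenge stands.
- The correlations are assumptions. The Outcome measures section says all measures refer to the past month, so baseline weekly consumption may be a close proxy for the others, and the gain would then be small.
- Entry requires heavy drinking on at least two occasions a month. This truncates the lower end of baseline HED and may weaken its correlation with later HED.
- The variance formula is for linear models. It does not carry over directly to ordered logistic or negative binomial regression. In the ordered logistic model the interval for the odds ratio need not become narrower; the gain is mainly in power.

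A reader might also infer that chance imbalance in the secondary baselines biases the estimates. The document does not support that. Randomisation keeps the comparison unbiased, and the interval already allows for chance imbalance, so this would be the same efficiency loss counted a second time. Nor is it right that own baseline is never adjusted for: the conditional rule can admit it. The accurate statement is that it is not prespecified.

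**Conclusion.** The point holds as one of efficiency. The primary models for HED, eBAC and negative consequences do not prespecify the outcome's own baseline, although it is recorded. The only route in is a rule that would act in about one trial in twenty for a given variable.

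In a linear model under the stated assumptions, the cost is 14–30% of residual variance, or a power of 80% where 86–92% was available. The wider grid shows that the gain could be a few per cent or considerably more, and the document does not allow a choice within that range. That the covariate is missing from the list is certain; how much it costs is not.

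It would be a mistake to conclude that the trial is underpowered or its main result affected. Weekly consumption is adjusted for its own baseline, and the sample size reproduces.

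**What to change.** State in the Statistical analyses section that each secondary model is adjusted for the baseline value of that same outcome, in addition to baseline weekly consumption, age, university and gender, and whether or not the arms differ significantly on it. Baseline HED category goes into the ordered logistic model, baseline eBAC into the eBAC model, and the baseline count into the negative consequences model.

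The cost is one sentence. It needs no new data and no more participants. The Trial status section says that recruitment had not begun at submission, so at that stage the change could be made before any outcome was observed.

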After completion of the baseline questionnaire, the students will be asked to provide their telephone number. Students will then immediately receive an SMS asking them to confirm their mobile phone number by responding “start”. All students who have confirmed their mobile phone number will be randomized to either the intervention or control group, SMS messages will be sent to each participant with information about which group they are allocated to. Figure 2 depicts a flowchart of the recruitment procedure of the study.

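### Baseline binge drinking, eBAC and negative consequences enter the primary model only if they happen to differ significantly between arms; they should be prespecified

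*Protocol article*

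**What the plan says.** Under Statistical analyses, every regression is run unadjusted and then "adjusted for weekly alcohol consumption at baseline, age, university and gender". The next sentence adds a conditional step: "If any of the baseline characteristics are significantly different between the two groups, further adjustment will be made to these covariates as well". The section then states: "The adjusted analyses will be the primary analysis". So the primary model has four fixed covariates plus whatever a baseline significance test brings in.

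The Baseline questionnaire section shows what else is available. After weekly consumption it lists "5) HED during the last month; (6) eBAC during the last month and (7) number of negative consequences caused by drinking alcohol", each over the past month. It also asks students to "state their goal for reducing their weekly alcohol consumption" and records relationship status. That makes five baseline variables outside the fixed set. All are asked before allocation. Participants and procedure says "After completion of the baseline questionnaire, the students will be asked to provide their telephone number", and only students who then confirm that number are randomised.

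Missing outcomes are handled at first by complete cases, "which assumes that the data are missing at random (MAR"). The plan then explores that assumption through the number of contact attempts, attrition by group, and the baseline characteristics of those who do and do not respond.

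**The concern.** In a randomised trial, a covariate earns its place by predicting the outcome. A significance test of baseline balance does not measure that. A strongly prognostic measure that is well balanced stays out, and an unhelpful one that is unbalanced by chance goes in. The form of the primary model is then known only after the data are examined.

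Two things are at stake. The first is precision: the target effect is only 0.15 SD, and HED and eBAC are further measurements of the behaviour that the single typical-week item measures. The second is missing data: in a complete-case regression, the missing-at-random assumption is conditional on the covariates in the model. If heavy binge drinkers drop out at different rates in the two arms, a model without that measure is harder to defend.

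**Working it through.** **The plan's own figure.** Inputs from the Power calculation section: 0.15 SD, 5% significance, 80% power, 80% follow-up. The tests are two-sided (Statistical analyses).
- Normal formula: 2 × (1.960 + 0.8416)² / 0.15² = 697.7, so 698 per arm. The t-test version gives 699, as stated.
- 699 / 0.80 = 873.75, so 874 per arm, as stated.
- The calculation uses the unadjusted SD, so it relies on no covariate.

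**How often the conditional rule fires by chance.** There are five unlisted baseline variables, each tested at 5% with no true difference.
- Independent tests: 1 − 0.95⁵ = 22.6%.
- Simulated with assumed common correlations of 0.3 and 0.5: 20.7% and 18.2%.
- If the goal is not counted as a baseline characteristic, four independent tests give 1 − 0.95⁴ = 18.5%.

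**Precision.** The documents give no correlations, so everything here is assumed. In a one-factor model, r is the correlation of latent baseline drinking with the outcome and λ² is the reliability of each measure:
- R² = r² S / (1 + S), with S = Σ λ² / (1 − λ²).
- Central case: r = 0.6; λ² = 0.70 for weekly consumption; λ = 0.7, 0.6 and 0.5 for HED, eBAC and consequences.
- Weekly consumption alone: S = 0.70/0.30 = 2.333; R² = 0.36 × 2.333/3.333 = 0.252.
- All four: S = 2.333 + 0.961 + 0.563 + 0.333 = 4.190; R² = 0.36 × 4.190/5.190 = 0.291.
- Fall in residual variance: 1 − 0.7094/0.7480 = 5.2%. This is worth 1398 × (0.7480/0.7094 − 1) ≈ 76 analysed participants.
- Power at 699 per arm, Φ(0.15/√(1 − R²) × √349.5 − 1.96): 0.9002 becomes 0.9146, a gain of 1.4 points.

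This set-up flatters the extra covariates. It assumes independent reporting errors, and that the baseline item predicts its own repeat only through the latent factor. Relaxing those two assumptions in the central case gives:

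| Same-item covariance | Error correlation among baseline items | Fall in residual variance |
|---|---|---|
| 0 | 0 | 5.2% |
| 0.05 | 0 | 3.3% |
| 0 | 0.1 | 3.5% |
| 0.05 | 0.1 | 1.8% |
| 0.05 | 0.2 | 0.8% |

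The four relaxed rows correspond to gains of about 0.2 to 1.0 power points. A favourable corner with independent errors (r = 0.7, weekly reliability 0.6, all three other loadings 0.7) gives R² of 0.294 and then 0.399, so 1 − 0.601/0.706 ≈ 15%. It needs a noisy baseline item and three strong companions that share none of its error.

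**Complete-case bias.** A linear simulation used 874 per arm, about 80% response, a baseline–outcome correlation of 0.5, one omitted covariate with partial R² of 0.02, 0.05 or 0.10, and 1,500 repetitions (simulation error 0.0012 SD). The true effect was −0.15 SD and the standard error about 0.046.

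| How non-response depends on the omitted measure | Bias without it (SD) |
|---|---|
| Equally in both arms (log-odds slope 0.5 per SD) | within 0.0013 of zero |
| Slopes differ by 0.5 between arms | −0.011, −0.016, −0.023 |
| Slopes differ by 1.0 between arms | −0.021, −0.033, −0.044 |

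With the covariate in the model, bias was within 0.002 SD throughout.

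**The case against.** The strongest defence is that the plan is already sound. It names an adjusted primary analysis in advance, includes the baseline value of the outcome (usually the best single covariate), and has a sample size that reproduces without any covariate gain. At an assumed baseline–outcome correlation of 0.5, power at 699 per arm is already about 90%. All of this stands, and it is why the gain is small. Eligibility also restricts the range of HED, since students must already binge at least twice a month, so its added information may be less than assumed.

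Three stronger readings are tempting, and the documents do not support them:
- A reader might infer that the plan leaves these measures out altogether. It does not; the conditional sentence lets them in. The criticism is of the entry rule.
- A reader might infer that the complete-case estimate is biased. In a linear model that needs non-response to depend on the omitted measures differently by arm, and nothing in the article shows this. Complete cases are also only the initial approach, and what follows the planned checks may be in an analysis plan that is not shown. Those checks do look at attrition by arm and at baseline differences by response separately, not jointly.
- A reader might infer that the precision is free. The article does not say that every baseline item is mandatory. In the central case, losing about 5.2% of participants to a missing covariate would cancel the gain.

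The calculations are for a linear model and do not cover the negative binomial option.

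**Conclusion.** The point holds as a modest improvement to a stated rule. The article contains no error or contradiction here. Covariate entry by significance test would change the primary model by chance in about 18–23% of trials with no true imbalance, counting five variables, and it ignores prognostic value.

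The expected precision gain from prespecifying HED, eBAC and consequences is roughly 0–5% of residual variance, or 0–1.4 power points. It rests wholly on assumed correlations, and only a favourable corner of those assumptions exceeds it. The benefit for missing data is conditional: about zero under equal dependence, and 0.011 to 0.044 SD (7% to 29% of the 0.15 SD target) under the arm-specific dependence simulated. No prognostic gain was shown for the goal, which probably overlaps with reported consumption, or for relationship status.

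**What to change.** In Statistical analyses, list baseline HED frequency, eBAC and number of negative consequences as covariates of the primary-outcome model alongside the four already named, whatever imbalance is observed. Delete the sentence that adds covariates after a significance test. The reduction goal and relationship status are optional. Add one line on how a missing baseline item is handled, so that the longer list does not remove participants from the analysis.

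The cost is a sentence or two of wording and a few degrees of freedom out of about 1,398 analysed. No new data are needed, and the sample size stays as it is. Overlap among the drinking measures makes their own coefficients hard to interpret, but it does not harm the estimate of the arm effect.

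### Baseline significance tests may add covariates to the primary model; the main cost is to the secondary outcomes, whose own baseline values enter only if imbalanced

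*Protocol article*

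**What the plan says.** All of the rule stands in the protocol article, Statistical analyses.

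- Regressions are first run unadjusted and "then will be adjusted for weekly alcohol consumption at baseline, age, university and gender". These four covariates are fixed in advance.
- The extension follows: "If any of the baseline characteristics are significantly different between the two groups, further adjustment will be made to these covariates as well".
- The next sentence gives this model its status: "The adjusted analyses will be the primary analysis".
- The tests that drive the rule open the section: "The baseline characteristics of responders will be compared between randomized groups using the chi-squared test or Fisher’s exact test", with t tests for means.
- The threshold comes from the closing sentence: "All analyses will be performed with two-sided tests with a 5% level of significance".

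The Baseline questionnaire section shows what the rule could add. Items outside the fixed set are relationship status, the baseline values of the secondary outcomes ("5) HED during the last month; (6) eBAC during the last month and (7) number of negative consequences caused by drinking alcohol") and a request that students "state their goal for reducing their weekly alcohol consumption". That makes five candidates, or four if the goal is not counted as a characteristic. Nothing in the article confines the extra adjustment to a sensitivity analysis.

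**The concern.** Randomisation is simple, with equal probabilities and fully automated (Randomisation section). Among all randomised participants, a baseline test therefore checks a hypothesis already known to be true, and a positive result is a chance event. What makes a covariate worth having is how well it predicts the outcome. A small p-value for imbalance says nothing about that. The rule can admit a weak predictor that happens to differ and leave out a strong one that does not.

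Two things are at stake. First, part of the confirmatory model is unknown until the baseline tests are run, which leaves it open to dispute. Second, the article collects baseline HED, eBAC and negative consequences. Each is plausibly a leading predictor of its own follow-up value, yet none is in the fixed set, and each enters its own model only about 5% of the time. HED raises a further point because it is analysed by ordered logistic regression. Odds ratios are not collapsible, so adding a prognostic covariate changes the quantity estimated as well as its precision. A chance test would help decide which odds ratio is reported.

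The population for the tests is also unclear, because the article does not say whether responders are those who answered at baseline or at follow-up. If follow-up is meant, an imbalance may reflect attrition as well as chance. The selected covariates could then differ by outcome, since the SMS and telephone follow-up stages ask only for the primary outcome (Participants and procedure).

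**Working it through.** **1. The plan's own figure.** Inputs from Power calculation: 0.15 SD, two-sided 5%, 80% power.

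n per arm = 2 × ((1.960 + 0.842)/0.15)² = 697.7, so 698 against the stated 699. Power at 699 is 80.07%. Follow-up of 80% gives 699/0.8 = 873.75, so 874 per arm and 1748 in total. The figures reproduce and are not in question.

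**2. How often the rule changes the model.** With k independent candidates tested at 5%, P(at least one positive) = 1 − 0.95^k.

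- k = 4: 1 − 0.8145 = 18.5%
- k = 5: 1 − 0.7738 = 22.6%

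The drinking measures are probably correlated. With assumed pairwise correlations of 0.3 to 0.7, simulation gives 18.0% to 15.4% for four candidates and 21.5% to 17.4% for five. The range overall is about 15–23%.

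**3. What it does to power and size.** Let R be the multiple correlation of the four fixed covariates with the outcome, and r the partial correlation of one further covariate given those four. Both are assumptions, as the article gives neither. For a continuous outcome at 699 per arm:

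- residual SD with the fixed four: s₀ = √(1 − R²)
- residual SD with the extra covariate: s₁ = s₀√(1 − r²)
- power = Φ(0.15/(s × √(2/699)) − 1.960), where √(2/699) = 0.0535

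Example, R = 0.3 and r = 0.5. With s₀ = 0.954, power is Φ(2.940 − 1.960) = 83.6%. With s₁ = 0.826, power is Φ(3.394 − 1.960) = 92.4%.

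Power under the rule was simulated from the large-sample normal distributions (2,000,000 draws per setting). The extra covariate is used only when its own imbalance test is significant.

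| R | r | Fixed four only | Rule | Extra covariate always in | Loss: always in minus rule |
|---|---|---|---|---|---|
| 0.5 | 0.1 | 89.9% | 90.0% | 90.2% | 0.2 |
| 0.5 | 0.3 | 89.9% | 90.3% | 92.4% | 2.1 |
| 0.6 | 0.1 | 93.9% | 94.0% | 94.1% | 0.1 |
| 0.6 | 0.3 | 93.9% | 94.2% | 95.7% | 1.5 |
| 0.3 | 0.3 | 83.6% | 84.0% | 86.9% | 2.9 |
| 0.3 | 0.5 | 83.6% | 84.8% | 92.4% | 7.6 |
| 0.6 | 0.5 | 93.9% | 94.7% | 98.2% | 3.5 |

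*Primary outcome.* Its own baseline is in the fixed set, so R of 0.5–0.6 with r of 0.1–0.3 is a reasonable range. The loss is about 0–2 points.

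*Secondary outcomes.* Their own baselines are outside the fixed set, so r of 0.3–0.5 is plausible. The loss runs from 1.5 points (R = 0.6, r = 0.3) to 7.6 points (R = 0.3, r = 0.5), or about 1–8. If the fixed covariates explained nothing (R = 0, r = 0.5) it would be 8.7 points, an outer bound.

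*Size under the rule.* It is 4.7–5.0% for r up to 0.3 and 4.3% for r = 0.5, never above nominal.

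**4. A less favourable assumption for the primary outcome.** A separate simulation kept baseline consumption in the model, gave four of the five candidates (all but relationship status) the same weight as baseline consumption, and set the joint multiple correlation at 0.3–0.6. Power under the rule was 83–90%, against 85–94% with all six covariates fixed, and size was 4.0–4.8%. The gap is wider because so much prognostic information was placed outside the fixed set.

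**The case against.** The strongest defence is that the rule is written in advance, has a stated threshold and looks neither at outcome data nor at the treatment effect, so it is not a choice among results. Four covariates are fixed, including the primary outcome's own baseline. On the article's own 5% threshold, roughly four trials in five would use exactly that fixed model. All of this stands. The primary model is partly unknown in advance, not wholly.

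A reader might go further and infer that the rule inflates false positives. It does not: size is at or slightly below 5% in every setting examined. A reader might also infer that the primary analysis loses most of the power adjustment can offer, say about 82% against 90–94%. Those figures arise when a strong predictor (partial correlation 0.5–0.6) is left to the rule and the fixed covariates earn no credit. The article puts baseline consumption in every adjusted model, so they do not describe its primary analysis.

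Two further criticisms carry little weight. Using t tests on skewed measures is immaterial with about 700 or more per arm. Forcing relationship status into every model is not supported either, since the article gives no prognostic basis for it.

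The defence does not answer why a chance imbalance should alter a confirmatory model at all, or why the baseline values of three secondary outcomes should be left to a 5% lottery.

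**Conclusion.** The concern holds as a weakness of pre-specification and, for the secondary outcomes, of efficiency. It is worth correcting and does not threaten the trial's validity.

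- About 15–23% of trials run under this rule would have their primary model altered by an imbalance test. This assumes four or five candidates and valid randomisation. If responders means follow-up responders, attrition may add to it.
- For the primary outcome the power at stake is about 0–2 points under the assumed correlations. The gain there is a model known in advance. Deleting the rule without adding covariates leaves power essentially where it is: in the R = 0.5–0.6, r = 0.1–0.3 rows, the fixed-four and rule columns differ by at most 0.4 points.
- For a secondary outcome the loss is about 1–8 points, depending on how much the fixed covariates already explain. This was computed for a continuous outcome with a 0.15 SD effect. It is only indicative for HED (ordinal) and for any outcome analysed by negative binomial regression.

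A separate analysis plan may already settle the covariates, but it is not shown. The finding concerns the rule as the article states it.

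**What to change.** 1. Delete the sentence that triggers further adjustment, or keep the extra adjustment only as a labelled sensitivity analysis.
2. Stop between-arm baseline tests from deciding any model. Describing baseline by arm is sufficient. The planned attrition checks serve another purpose and can stay.
3. State the covariates for every adjusted model now: baseline weekly consumption, age, university and gender, plus the baseline value of the outcome itself in the HED, eBAC and negative-consequences models. The primary model then contains exactly the four core covariates.
4. Say which participants are meant by responders wherever baseline is summarised.

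The cost is one sentence removed and one list extended. The baseline items are already in the questionnaire, and the sample size stays at 699 analysed and 874 randomised per group. The Trial status section says recruitment had not begun at submission, so the list could have been fixed before any data existed. If a separate analysis plan already fixes a list, the two texts should be brought into agreement.
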